#### Treatment as usual (TAU)

Patients included in the current study will undergo the usual treatment provided by their addiction treatment center (TAU). These can vary from short individual behavioral treatment intervention, inpatient treatment, Community reinforcement therapy, or extensive multidimensional therapy (like MDFT) with attention to psychological, social, relation, financial, and medical problems. During the study the psychological interventions applied will be monitored. For the historical control group, reports on the adjunct psychological treatment interventions applied are unavailable.

### Outcome and instruments

#### Primary outcome measures

The primary study outcome is the relapse rate, in other words the level of GHB use as indexed by the total number of abstinent days, the duration of continued abstinence after detoxification (CAD), time before relapse, and intensity of substance use over a period of 3 and 6 months (Timeline Follow-back Method).

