**Methods/Design:**

In an open label non-randomized trial treatment with baclofen to a maximum of 60 mg/day will be compared with treatment as usual (TAU) in recently detoxified GHB dependent patients (n = 80). The primary outcome measure will be the level of GHB use. Secondary outcome measures are craving levels, psychiatric symptom levels and quality of life. Questionnaires will be administered during 12 weeks of baclofen treatment and at follow-up (six months after the start of treatment).

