#### Sample size calculation

To date, there are no published studies on the effect of baclofen on relapse in GHB dependent patients. Therefore, we used the results of previous studies on the effect of baclofen in alcohol dependent patients and our previous work on GHB dependence, in order to estimate the required sample size. Two RCTs showed that baclofen was superior to placebo in increasing abstinence rates in alcohol dependent patients: 70% (14 out of 20) versus 21% (4 out of 19) within a period of 30 days [29] and 71% (30 out of 42 p) versus 29% (14 out of 42) within a period of 12 weeks [30]. These results indicate a potential increase in abstinence of 42–49% with baclofen treatment for alcohol dependence. Results of the previous national GHB project stated that 36% of the patients succeeded to avoid relapse in GHB within a period of 3 months after detoxification without any medical interventions [20]. Therefore, we will consider a percentage of importance difference in baclofen effect in the GHB dependent participants of 34% between the Baclofen + TAU group and the TAU only or the matched control group with an expected abstinence rate with baclofen of 70% as in the alcohol studies and of 36% without baclofen.

We used the following formula comparing two proportions to calculate the sample size, n = [(Zα/2 + Zβ)^2^ × {(p1 (1-p1) + (p2 (1-p2))}] / (p1 - p2)^2^, n = [(1.96+ 0.84)^2^ × {(0.7 (1–0.7) + (0.36 (1–0.36))}] / (0.34)^2^, according to [name] sample size calculator, Exeter Initiative for Statistics. The calculation estimates that the minimal total samples size of 30 patients per group would be sufficient to detect a clinical difference of 34% in two-tailed z-test of proportions (α = 0.05, β=0.80). In the alcohol studies and our previous work with GHB inpatients an attrition rate of 13–15% was reported. We anticipate a slightly higher drop-out rate of 25%, due to the outpatient component of the baclofen treatment. Therefore we will include 40 participants in the baclofen treatment group.

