### Statistical analyses

Descriptive analysis will be executed for all measurements and will include the mean, SD and frequencies of events with confidence intervals. Descriptive statistics will be used to compare the basic characteristics of the participants in the experimental group and the control groups. To assess any difference in relapse rates between the experimental group and the control groups (TAU group and matched historical group) at 3 month after detoxification Pearson Chi-squared test will be used for the dichotomous abstinence rates. ANOVA will be carried out on continuous variables, such as the total number of abstinent days, the maximum duration of continued abstinence, time before relapse (relapse defined as ≥ 3 times GHB use per day, for 2 subsequent days), and level of substance use over a period of 3 months. At 6 months period participants who continued baclofen will be compared to those who have stopped with baclofen (after 3 month) on relapse into GHB abuse or abstinence corrected for craving. The numbers of patients maintaining abstinence will be analysed with the intention-to-treat principles. The difference in craving will be analysed by MANCOVA at 3 months between groups (abstinent experimental versus abstinent TAU or relapsed TAU) with DDQ and VAS craving as dependent variables and corrected for craving levels immediately after detoxification. The change in craving in time during the baclofen treatment will be analysed via repeated measures MANOVA. By means of MANCOVA at 6 months after detoxification the difference in craving among participants who are still using baclofen and those who have discontinued baclofen will be analysed corrected for craving after 3 months. The effect of baclofen on the psychiatric symptoms levels (DASS, MINI) and also quality of life (EQ–5D) will be analyzed similarly as for craving at 3 and 6 months. The effects of the different TAU approaches as potential confounders will be tested in a sensitivity analyses (changing one-factor-at-a-time) in an linear regression including TAU per center as covariates.

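### The primary outcome is worded as relapse, abstinence and level of use without one being chosen, so the same data can support different conclusions

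*Protocol article*

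**What the plan says.** The outcome is worded differently in different sections of the protocol article.

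- **Abstract, Methods/Design:** "The primary outcome measure will be the level of GHB use".
- **Aims and hypotheses:** the primary hypothesis concerns lower relapse rates.
- **Primary outcome measures:** "The primary study outcome is the relapse rate, in other words the level of GHB use". Four indices follow: days abstinent, length of unbroken abstinence, time to relapse, and how heavily GHB is used. They are to be taken at both 3 and 6 months. None of the four is put first, and neither time point is named as primary.
- **Statistical analyses, purpose of the test:** "To assess any difference in relapse rates between the experimental group and the control groups". The comparison is set at 3 months after detoxification. The Pearson chi-squared test that follows is applied to dichotomous abstinence rates, and ANOVA to the continuous indices.
- **Statistical analyses, definition:** "relapse defined as ≥ 3 times GHB use per day, for 2 subsequent days". This stands in a parenthesis attached to time before relapse. Abstinence has no definition anywhere.
- **Sample size calculation:** the control rate comes from the earlier national project, where "36% of the patients succeeded to avoid relapse in GHB within a period of 3 months". The calculation then uses "an expected abstinence rate with baclofen of 70% as in the alcohol studies and of 36% without baclofen".

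Two control groups are named, concurrent TAU-only patients and a matched historical group. Neither is given precedence.

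**The concern.** Relapse, abstinence and level of use are three different quantities. On the ordinary reading of abstinence as no use, relapse as defined is not its complement. Someone who uses GHB twice every day for 3 months is not abstinent, yet never meets the relapse definition. Such patients are successes on a relapse-free endpoint and failures on an abstinence endpoint.

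The protocol's own rationale makes this group relevant. The Background proposes baclofen as a longer-acting substitute for GHB, and the Discussion says the substitution hypothesis will be tested. Use that continues at a lower level is therefore a plausible place for the arms to differ.

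The dichotomous proportion on which the trial is sized is not among the four indices listed under Primary outcome measures. In an open-label, non-randomised study, a primary result that can be picked after the data are seen weakens whatever is claimed from it.

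**Working it through.** **1. The plan's own sample size.** Inputs from Sample size calculation: p1 = 0.70, p2 = 0.36, Z values 1.96 and 0.84, dropout 25%.

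n = (1.96 + 0.84)² × (0.70×0.30 + 0.36×0.64) / 0.34² = 7.84 × 0.4404 / 0.1156 = 29.87, so 30 per group.

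With dropout: 30 / (1 − 0.25) = 40.

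Both figures reproduce. What is unclear is what the two proportions measure: 70% is abstinence in alcohol trials, and 36% is avoidance of relapse in GHB patients.

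**2. Can the choice of endpoint change the result?** The documents do not give the share of patients who use without relapsing, so the shares below are assumptions. Set 36% abstinent in both arms, 40 per arm, with use short of relapse in 10% of TAU patients. TAU is then 36% + 10% = 46% relapse-free. Let that share be larger on baclofen. Two-sided Pearson chi-squared at 0.05, without continuity correction:

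| Gap in use short of relapse | Relapse-free, baclofen vs TAU | Rejections, relapse-free | Rejections, abstinence |
|---|---|---|---|
| 5 points | 51% vs 46% | 8% | 5% |
| 10 points | 56% vs 46% | 16% | 5% |
| 15 points | 61% vs 46% | 29% | 5% |
| 20 points | 66% vs 46% | 46% | 5% |

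A single constructed data set with 30 per arm shows the same thing. Baclofen: 9 abstinent, 12 using without relapse, 9 relapsed. TAU: 10, 1 and 19.

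- Relapse-free, 21 vs 11: X² = 60 × (21×19 − 9×11)² / (32×28×30×30) = 6.70, p = 0.010.
- Abstinent, 9 vs 10: X² = 60 × (9×20 − 21×10)² / (19×41×30×30) = 0.077, p = 0.78.

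**3. False-positive risk when nothing is ranked.** There are five candidate measures: the four indices and the dichotomous proportion. The text does not say whether the control groups are compared pairwise or in one overall test, so both counts are shown. Test statistics are taken as multivariate normal, each tested two-sided at 0.05. The correlation between measures is assumed to be 0.8 to 0.3. The correlation between the two control comparisons is assumed to be 0.5, because they share the baclofen arm.

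| Tests | Chance of at least one false positive |
|---|---|
| One measure, two control groups | 9% |
| Five measures, one test each | 13% to 21% |
| Five measures, each against both controls (ten tests) | 22% to 35% |

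The independence figure for ten tests, 1 − 0.95¹⁰ = 40%, does not apply because of the shared arm.

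**4. Which comparison the schedule supports.** Table 2 marks Timeline Follow-back for both concurrent groups at week 12 and for the baclofen group only at week 24. On that schedule, a comparison with concurrent TAU on these indices is possible at 3 months but not at 6.

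**The case against.** **A consistent reading exists.** Abstinence is undefined, and the article uses avoidance of relapse and abstinence for the same 36%, so the dichotomous variable may simply be relapse-free, yes or no. The chi-squared test at 3 months is listed first and matches the type of proportion used for sizing, so it looks like the lead analysis. This stands as a possible intention. But the text never says it, does not place that proportion among the primary indices, and does not rank it above them.

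**The study is explorative.** The Discussion says so, and a favourable result is meant only to justify controlled trials. That lowers the stakes and the severity. It does not settle which quantity is primary, and the article still states a primary hypothesis and a powered two-sided test.

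**Multiplicity rules may be in an analysis plan that is not shown.** This is fair, and their absence is not the point. The point is that the sections shown name different quantities as primary.

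**Stronger readings that the documents do not support.** A reader might infer that the endpoints will give opposite answers. In the 20-point scenario above, significant results in opposite directions arise in only about 0.04% of simulated trials. Constructing one takes an extreme split. With 30 per arm, 17 vs 0 patients using without relapse and 4 vs 11 abstinent, relapse-free is 21 vs 11 (p = 0.010 for baclofen) and abstinence favours TAU (p = 0.037). A reader might also infer that the trial is underpowered. If abstainers are a subset of the relapse-free, control abstinence cannot exceed 36% and the baclofen relapse-free rate cannot fall below its abstinence rate. For a given 70%, the 34-point difference is therefore, if anything, conservative.

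**Conclusion.** The concern holds as a contradiction in the wording of the primary outcome. Relapse rate and level of use are equated, the test is introduced for one quantity and run on another, and the sample size relabels avoidance of relapse as abstinence. The same data can therefore lead to different conclusions, most likely a significant result on one endpoint and none on the other.

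How often this would happen cannot be stated. It depends on the share of patients who use without relapsing, which the documents do not give, and on abstinence meaning no use. The 8% to 46% range illustrates assumed shares and does not forecast the trial. The false-positive figures likewise rest on assumed correlations and on which test count applies. Whether the source of the 36% used the same relapse definition cannot be seen.

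This should be fixed. It is not graded higher because the authors declare the design explorative.

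**What to change.** Name one dichotomous primary outcome with one definition, at 3 months after detoxification, for baclofen plus TAU versus concurrent TAU. Freedom from relapse by the definition already in Statistical analyses is one option, and it matches the stated aim. Complete abstinence would also serve if it is defined and used throughout.

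- Use the chosen outcome in the abstract (Methods/Design and Discussion), Aims and hypotheses, Sample size calculation, Primary outcome measures and Statistical analyses.
- Define abstinence explicitly.
- Make the remaining indices secondary and the historical comparison supportive.
- In Sample size calculation, state that the 70% is an abstinence rate from alcohol trials, used as an assumption. Choosing a relapse-free endpoint does not remove that mismatch.
- Re-express the 36% under the chosen definition if the historical data record frequency of use; the article says only that follow-up data exist. If they do not, state the mismatch.

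The cost is wording in about six places, plus some work on the historical data where these allow it. No new visits or measurements are needed. The downside is that a single result carries the claim.

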## Methods and Design

### Study design

The design is of an open label non-randomized controlled clinical study in six addiction care facilities in the Netherlands. The study is part of the Dutch national GHB Monitor 2.0 and data collection will take place between May 2014 and December 2015. After successful detoxification of GHB, patients will receive either baclofen on top of treatment as usual (TAU + baclofen) or treatment as usual (TAU) only. Assignment is based on in- and exclusion criteria and on patient preference (informed consent).

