### Study intervention

#### Baclofen intervention

Clinical trials on baclofen for alcohol dependence treatment have used baclofen at a dose of 30 mg ⁄d [29-31] over 30 to 120 days. This is within the low therapeutic range for muscle spasms. However, Garbutt and colleague’s [32] suggested that 30 mg of baclofen per day may be an insufficient dose for some patients to achieve abstinence. Additionally, baclofen effectiveness for GHB dependence could be smaller, since tolerance may occur due to recent abuse of GHB and a possible substitution function (as treatment will be started immediately after detoxification).

Based on these results and the unpublished results of a small dose finding experimental treatment study in our treatment center, where patients reported limited effect of baclofen 30 mg per day, we decided to administrate a dose of 45 mg to a maximal dose of 60 mg per day orally to avoid the risk of (co) intoxication. In this study baclofen will be administrated orally three times daily as usually recommended [22] and started with a total dose of 15 mg per day. During the first 10 days baclofen will be gradually increased with 15 mg per day every 3 days up to the chosen minimum dose of 45 mg, or a maximum dose of 60 mg in case no effect is reported at 45 mg after 2 weeks. This dose will subsequently be maintained for a period of 10 weeks. Successively, baclofen will be tapered off to 0 mg in 2 weeks (see Table 1). Patients will be asked to avoid abrupt termination of baclofen and will be guided by their physician to avoid complications of baclofen withdrawal. Patients who wished to continue the baclofen treatment will be offered an outpatient counselling and medication by their physician for another 3 months.

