**Table 1 Tab1:** **Baclofen dose in mg/week**

**Week**	**1**	**2**	**3**	**4**	**5**	**6**	**7**	**8**	**9**	**10**	**11**	**12**	**13**	**14**	**15**
Doses a day	15–30	45–60	45/60	45/60	45/60	45/60	45/60	45/60	45/60	45/60	45/60	45/60	30–45	15–30	15–0

Compliance will be assessed based on self-report, urine test for GHB, and empty pill counts. The physician will make use of the BRENDA method, a psychosocial program designed to enhance medication and treatment compliance [33,34]. In case of GHB use during baclofen treatment, participants are expected to contact the research physician. In case of relapse, immediate cessation of treatment will be considered to avoid intoxication hazards.

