**Table 2 Tab2:** **Time measurements**

**Week**	**0**	**1**	**2**	**3**	**4**	**5**	**6**	**7**	**8**	**9**	**10**	**11**	**12**	**13**	**14**	**15**	**24**
Measurement	**T0**-baseline	**T1**											**T2**				**T3**
Mate section	xx												xx				x
EQ–5D	xx												xx				x
DASS	xx												xx				x
Mini-plus	xx												xx				x
Blood	xx						x						x				
Urine	xx						x						xx				x
Medical consult	2x	2x	2x	x	x			x			x		x	x	x		
Baclofen (mg)	0	15–30	45– 60											30–45	30–15	15–0	0
Baclofen Side effect	x	2x	2x	x	x			x			x		x				
VAS	xx	x	x	x	x			x			x		xx				x
DDQ	xx	x	x	x	x			x			x		xx				x
Baclofen withdrawal checklist														x	x	x	
Timeline follow back													xx				x

xx = baclofen group and control group TAU only.

x = baclofen group.

T0 = end of GHB detoxification.

T1 = start baclofen treatment.

T2 = follow-up TAU only and end of baclofen therapy.

T3 = follow-up baclofen group.

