## Discussion

This study protocol presents the design of an open label clinical trial evaluating the efficacy of baclofen to prevent relapse, reduce craving and anxiety, and to assess the safety profile of baclofen in GHB dependent patients. To date, there are no reports on the potential of baclofen to prevent relapse in GHB dependent patients. We expect that baclofen will increase abstinence rates, reduce craving and will be well tolerated. In addition, baclofen may improve psychiatric symptoms such as anxiety and depression, as suggested in several clinical trials in alcohol-dependent individuals [29,30,46].

Several risks of baclofen use are taken into account in the current study. In patients with neuropsychiatric disorders, such as schizophrenia, severe depression, mania, Parkinson’s disease and cerebrovascular diseases, exacerbations of these conditions may occur, when the dose of baclofen is rapidly increased. It may lower the threshold for seizures in epileptic patients [42]. To limit these risks in the current trial, baclofen will be uploaded gradually, over a period of minimally 10 days. Moreover, patients previously diagnosed with any of the mentioned diseases will be excluded from the study.

Abrupt discontinuation of baclofen, when used for several months, can be associated with a withdrawal syndrome which resembles benzodiazepine and alcohol withdrawal. Several symptoms are reported such as hallucinations, fever, confusion, delirium, agitation, insomnia, and muscle stiffness and spasms [47]. Therefore, patients will be advised to taper down slowly when discontinuation is needed.

Intoxication with baclofen has been reported in doses above 100 mg [48]. This risk increases if patients combine baclofen with GHB. Intoxication is not expected when baclofen is administered at a low dose (<30 mg per gift), as applied in the current study. Patients will however, be informed repeatedly of this potential risk and the treatment will be discontinued immediately in case of relapse.

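### The primary outcome of this open-label trial is named from self-report alone, and a treatment consequence of relapse is stated only for the baclofen group, so group-dependent under-reporting is plausible and unchecked

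*Protocol article*

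**What the plan says.** - **Blinding.** Study design: "The design is of an open label non-randomized controlled clinical study in six addiction care facilities in the Netherlands". Assignment also depends on patient preference.
- **Outcome source.** Primary outcome measures lists several indices of GHB use and names one source: "intensity of substance use over a period of 3 and 6 months (Timeline Follow-back Method". Statistical analyses applies a Pearson chi-squared test to 3-month abstinence and ANOVA to the continuous indices. It defines relapse by a number of uses per day on consecutive days. No urine rule appears in either section.
- **Disclosure on baclofen.** The text after Table 1 says: "In case of GHB use during baclofen treatment, participants are expected to contact the research physician".
- **Consequence of relapse on baclofen.** The same text says: "In case of relapse, immediate cessation of treatment will be considered to avoid intoxication hazards". The Discussion says: "the treatment will be discontinued immediately in case of relapse". Neither the TAU section nor any other states a consequence of relapse for TAU-only patients.
- **Continuation.** Baclofen intervention: "Patients who wished to continue the baclofen treatment will be offered an outpatient counselling and medication by their physician for another 3 months".
- **Urine.** The only stated purpose of the GHB urine test is compliance: "Compliance will be assessed based on self-report, urine test for GHB, and empty pill counts". The urine row of Table 2 is marked xx at weeks 0 and 12, and x at weeks 6 and 24. The key reads "xx = baclofen group and control group TAU only", and a single x is the baclofen group only. Timeline Follow-back is xx at week 12 and x at week 24.

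**The concern.** Patients know their treatment and supply the outcome themselves. On the stated rules, a baclofen patient who admits relapse puts the current treatment at risk. The document attaches no such cost to the same admission by a TAU patient. If this leads relapsed baclofen patients to under-report more often than relapsed TAU patients, reported abstinence shifts towards baclofen without any drug effect.

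This is outcome misclassification that depends on treatment. Matching, age and gender as covariates, and the sensitivity analysis on TAU do not address it. The limitations paragraph names lack of randomization, lack of placebo and varying TAU, but not reporting.

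The point goes beyond detail that a condensed article leaves out. The article positively names recall as the outcome source and positively assigns the GHB urine test to compliance.

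**Working it through.** **Inputs from the protocol article (Sample size calculation):** expected abstinence 70% with baclofen and 36% without; two-sided 5% level; 80% power (Zβ = 0.84); 30 per group before drop-out; 25% drop-out; 40 in the baclofen group. The abstract gives 80 in total.

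**The plan's own figure reproduces:**

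(1.96 + 0.84)² × (0.70 × 0.30 + 0.36 × 0.64) / 0.34² = 7.84 × 0.4404 / 0.1156 = 29.87, rounded up to 30. Then 30 / 0.75 = 40.

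**Inputs assumed, because the documents give none:** c, the share of relapsed baclofen patients who report abstinence, and d, the same share in TAU.

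**Model with an inert drug:** true abstinence is 36% in both groups. Reported abstinence is 0.36 + 0.64c on baclofen and 0.36 + 0.64d on TAU.

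**False-positive rate:** the sum, over all pairs of counts (x, y), of the two binomial probabilities wherever |z| > 1.96, with z = [(x − y)/n] / √[P(1 − P) × 2/n] and P = (x + y)/(2n). This is the uncorrected Pearson test.

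| c | d | Reported, baclofen vs TAU | 30 per group | 40 per group |
|---|---|---|---|---|
| 0 | 0 | 36.0% vs 36.0% | 4.8% | 4.9% |
| 10% | 0 | 42.4% vs 36.0% | 7.8% | 9.2% |
| 20% | 0 | 48.8% vs 36.0% | 17.0% | 22.2% |
| 30% | 0 | 55.2% vs 36.0% | 32.6% | 42.9% |
| 20% | 10% | 48.8% vs 42.4% | 8.0% | 9.7% |
| 30% | 10% | 55.2% vs 42.4% | 17.2% | 22.5% |
| 20% | 20% | 48.8% vs 48.8% | 5.2% | 5.7% |
| 40% | 40% | 61.6% vs 61.6% | 4.8% | 5.1% |
| 10% | 20% | 42.4% vs 48.8% | 8.0% | 9.7% |

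Where c exceeds d, nearly all the excess favours baclofen (at c = 20%, d = 0 and 40 per group, 22.1 of the 22.2 points). In the last row it runs against baclofen. What matters is the difference between groups, not concealment as such.

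The whole planned 34-point difference would need c = 0.34 / 0.64 = 53% with d = 0, which is an extreme case.

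**What a partial check buys.** If urine catches a share s of concealers, reported abstinence on baclofen becomes 0.36 + 0.64c(1 − s). With c = 20%, d = 0 and 40 per group, the rate falls from 22.2% to 18.9% (s = 10%), 14.6% (s = 25%) or 9.2% (s = 50%). The values of s are also assumptions. The Background gives a plasma half-life of about 30 to 60 minutes, so s may be small.

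**The case against.** Several stronger readings are tempting, and the documents do not support them.

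- **That a TAU patient loses nothing by reporting relapse.** No passage says so. TAU varies by centre and can include inpatient care, and its response to relapse is not described. What can be said is that no consequence is stated.
- **That a baclofen patient who relapses forfeits the further 3 months.** The continuation is offered to those who want it and is not tied to abstinence.
- **That treatment is always lost on relapse.** The intervention text says stopping is considered; only the Discussion makes it automatic.
- **That the bias must favour baclofen.** The baclofen group has more medical contacts and an additional week-6 urine sample, either of which could deter concealment. Week 12 is also labelled the end of baclofen therapy, with the taper following, so less treatment remains at stake when the recall is taken. Research assistants assess both groups identically. Relapses hidden from the physician earlier could still carry over into the recall, but that is conjecture.
- **That an objective check of both groups is already in hand.** Table 2 says only that urine is taken. That the TAU sample is tested for GHB is an inference.
- **That urine would settle the matter.** One sample cannot verify 12 weeks.

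It can also be said that the study calls itself explorative and leaves firm conclusions to randomized trials, and that a fuller document may hold a rule for using urine. The explorative purpose lowers the stakes. It does not answer the point, because a positive result is meant to justify such trials. On the possible rule, the article itself fixes recall as the outcome source and compliance as the role of urine.

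These objections limit the claim about size and direction. They leave standing the reliance on self-report and the one-sided stated consequence.

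**Conclusion.** The concern holds in a limited form. The primary outcome rests on recall by unblinded patients, and the only stated treatment consequence of admitting relapse falls on the baclofen group. Differential under-reporting in favour of baclofen is plausible; its size and net direction cannot be known from the documents.

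With 36% true abstinence in both groups and 20% assumed concealment on baclofen, the false-positive rate is 17% to 22% with no TAU concealment and 8% to 10% with 10% TAU concealment. With equal concealment it stays near 5%. These figures illustrate sensitivity and do not predict the trial's error rate.

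The plan should be changed, because a partial check can be built on a sample already scheduled and would show whether discordance differs between the groups.

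**What to change.** 1. State that the week-12 urine is tested for GHB in both concurrent groups, with a cut-off fixed in advance above endogenous levels, since the Background describes GHB as related to endogenous GABA metabolism.
2. In the chi-squared comparison of baclofen with concurrent TAU, count a positive week-12 urine as not abstinent.
3. Report by group the share of self-reported abstainers with a positive urine.
4. Show the result on self-report alone as a sensitivity analysis.
5. Keep the existing relapse definition for time to relapse. A positive sample contradicts abstinence but does not show relapse as defined.
6. Leave the week-6 urine out of the comparison, because only the baclofen group gives it.
7. Keep the historical-control comparison on self-report in both groups, so that each comparison uses one outcome definition.
8. Reconcile the two statements on what happens to baclofen treatment after relapse, and add reporting bias to the limitations.

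**Cost:** outcome wording, one table, and GHB assays on TAU samples if these are not already planned; no extra visits, samples or patients. **Downside:** urine detects recent use only, so the check reduces the bias without removing it, and it cannot cover the historical controls.
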